## Abstract

**Background:**

Chronic obstructive pulmonary disease (COPD) is a common disease associated with premature death. Tobacco exposure is the main risk factor, but lower socioeconomic status, early life insults, and occupational exposures are also important risk factors. Socially marginalized people, facing homelessness, substance use disorder, and mental illness, are likely to have a higher risk of developing COPD, and, furthermore, experience barriers to healthcare access and consequently poorer outcomes.

**Objective:**

This study aims to assess COPD prevalence and the impact of opportunistic screening among hospitalized patients who are in contact with hospital social nurses. These patients constitute a group of patients with a high prevalence of psychiatric and somatic diseases, substance use, low life expectancy, and are socially marginalized.

**Methods:**

The present prospective longitudinal study includes a clinical examination at baseline. Participants will have spirometry done and be interviewed regarding risk factors, socioeconomic conditions, and respiratory symptoms. The 5-year follow-up assessment incorporates data from baseline and register data over the 5 years, including information on morbidity, use of COPD medication, hospital contacts, mortality, and socioeconomic factors.

**Anticipated results:**

Referral for further diagnostic work-up and management after the screening, including COPD treatment and smoking cessation support, is expected to improve survival rates. The study is still enrolling patients.

**Trial registration:**

The study is registered at ClinicalTrials.gov , NCT04754308 with study status: “enrolling”.

**Supplementary Information:**

The online version contains supplementary material available at 10.1186/s12890-024-02927-9.

## Take home message

COPD may disproportionately affect socially marginalized patients causing a substantial disease burden. By opportunistic screening, we aim to assess COPD prevalence to facilitate early diagnosis and treatment, and by that potential outcome.

## Introduction

### Background and rationale

Chronic obstructive pulmonary disease (COPD) is a progressive, life-threatening condition caused predominantly by smoking, and includes symptoms such as breathlessness and cough [1]. The gradual onset of the disease, with as many as 85% of patients being diagnosed very late in its course [2, 3], emphasizes the critical importance of early detection for reducing disease progression and, consequently, morbidity [4]. Smoking cessation is the most important intervention to prevent the disease from worsening, and access to appropriate treatment is essential for better symptom control and, by that, improved quality of life [2, 5].

In the search for better ways to identify COPD cases, scholars have explored various methods [6]. However, the studies so far have been diverse in design and outcome, hindering conclusive findings [6]. Nevertheless, a recent study from Canada which actively looked for cases, suggests that there is a potential for early diagnosis and improved long-term prognosis [7]. While routine COPD screening in asymptomatic adults is not recommended in the U.S., screening high-risk and/or symptomatic patients aligns with international recommendations [1]. In our study, we introduce case finding in expected high-risk patients admitted to Danish hospitals.

Nation-wide studies have found social inequality in the occurrence of COPD [2], and even showing a social gradient within the range of deprivation [8]. In Denmark, COPD is the disease that contributes most to social inequality in health [6]. Socially marginalized individuals in Denmark, such as those affected by homelessness, substance use, harmful alcohol use, mental illness, and poverty, have a higher disease burden and worse well-being than the general population [9]. They also have overuse of healthcare services, including emergency departments, on-call doctors, general practitioners, and higher somatic/psychiatric admission rates [10], yet despite their increased contact with the healthcare system, they have significantly higher mortality rates, as socially marginalized people die on average 17 years earlier than the background population [9].

The Danish healthcare system is 100% tax-financed, with free access to healthcare for all citizens. However, there is increasing inequality in treatment outcomes [9, 11]. With the overall aim of reducing healthcare inequality, Danish hospitals have employed social nurses.

Social nurses are registered nurses, that provide support to socially marginalized patients throughout their hospitalization, promote treatment equity, and ensure the best possible treatment outcomes [12–14]. These nurses, who have specialized knowledge and practical experience in working with socially marginalized citizens, originate from positions such as street nurses, shelter nurses, and nurses in substance maintenance treatment clinics.

Previous studies have revealed a strong association between low socioeconomic status (SES) and the presence of COPD [2]. Although individuals from socially marginalized backgrounds tend to have more frequent hospital visits and higher mortality rates [9, 10] there is a lack of available studies examining healthcare utilization, risk factors, and mortality related to COPD in patients in contact with social nurses - a patient group that represents some of the most disadvantaged individuals in Denmark. This gap in knowledge highlights the need for comprehensive investigations to facilitate a more profound understanding of the issue, as that is likely to have significant implications for global healthcare strategies aimed at addressing the multifaceted challenges faced by socially marginalized populations.

We hypothesize that socially marginalized patients in contact with social nurses, have at least a twofold higher prevalence of COPD compared to the general population, as smoking is highly prevalent in lower income groups and is adding to socioeconomic inequalities [15, 16].

### Objective

The objective of the present study is 1) to investigate and describe the prevalence of COPD among hospitalized marginalized patients being in contact with social nurses and 2) to examine the 5-year impact of opportunistic screening for COPD and referral for health care management on outcome.

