### Study design

This is a prospective longitudinal study with 5 years follow-up from the date of inclusion.

The power calculation is based on the assumption that the prevalence of COPD will be twice the prevalence in the Danish background population (4.3%). With a power of 80% and a significance level of 0.05, a sample comprising 511 patients is required.

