#### Five-year follow-up outcome measures

At follow-up, we will report on whether:Opportunistic screening for COPD by social nurses has an impact on the rate of hospital contacts. This is assessed by examining the number of hospital contacts per person year within each year of the 5-year follow-up (both outpatient visits and hospitalizations) with a diagnosis related to COPD for three patient groups: (1) the group with no previous COPD diagnosis, impaired lung function at screening, and who underwent further assessment, (2) the group of patients with previous diagnosed COPD and impaired lung function at screening, and (3) the group with no previous COPD diagnosis, impaired lung function at screening, and who declined further assessment (Fig. 1).Opportunistic screening for COPD by social nurses has an impact on the use of COPD medication. This is assessed by examining number of prescriptions filled for COPD medications for two patient groups: (1) the group with no previous COPD diagnosis, impaired lung function at screening, and who underwent further assessment, and (2) the group of patients with previous diagnosed COPD at (Fig. 1). The reporting of medication will be organized into distinct categories, encompassing bronchodilators, corticosteroids, rescue medications, and maintenance therapies. Within each of these groups, the dosage prescribed or dispensed will be quantified.

Previous or no previous COPD diagnosis is assessed by the questionnaire at the time of screening as a patient-reported outcome. The lung function impairment is defined as FEV1/FVC ratio < 0.7. In the reporting, patients are stratified into groups with confirmed and non-confirmed COPD diagnosis.

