### Statistical considerations

Continuous variables will be presented as mean with standard deviation if the variable can be assumed to be normally distributed, otherwise, the median and interquartile range will be presented. Categorical variables will be presented with frequencies for each level and their corresponding percentages.

The prevalence of COPD in the study population will be compared to the prevalence in the Danish general population using an unadjusted test of the ratio of proportions, with a normal approximation of the logarithm of the ratio.

Since participants can die or otherwise drop out during the follow-up period, participants contribute with different follow-up lengths. The number of contacts in the follow-up period will therefore be reported as a rate (contact rate) of the number of contacts divided by the follow-up length, that is as contacts per year.

The healthcare contact rate will be compared among the three previously described COPD groups: undiagnosed COPD at inclusion who underwent further assessment, undiagnosed COPD without further assessment, and previously diagnosed COPD at inclusion, using a Poisson regression model. The model will include potential confounders as independent variables in addition to the COPD groups.

Sub-analyses for the rate of acute contacts and outpatient contacts will be conducted using models constructed in the same way as for all contacts.

Medication usage as a rate: number of prescriptions per year. Likewise, a Poisson regression model will be used to compare the rates among the COPD groups. However, the groups will be divided into no COPD versus diagnosed COPD. We will employ rigorous control for potential confounders. Specifically, age, smoking history, and comorbidities will be included as covariates in our models.

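### The 5-year aim is framed as the impact of screening, but every patient in the planned comparison was screened and referred, so no contrast estimates a screening effect

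*Protocol article*

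**What the plan says.** The Objective section sets as its second aim "to examine the 5-year impact of opportunistic screening for COPD and referral for health care management on outcome". Under Five-year follow-up outcome measures, the study will report whether "Opportunistic screening for COPD by social nurses has an impact on the rate of hospital contacts", and it asks the same about COPD medication. The Abstract adds that referral and management after screening "is expected to improve survival rates".

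The design is given in one sentence: "This is a prospective longitudinal study with 5 years follow-up from the date of inclusion". Hospital contacts are to be compared among three groups:

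- Group 1 is defined as "1) the group with no previous COPD diagnosis, impaired lung function at screening, and who underwent further assessment".
- Group 2 consists of people who reported an earlier COPD diagnosis and whose spirometry was also impaired when they were screened.
- Group 3 is defined as "3) the group with no previous COPD diagnosis, impaired lung function at screening, and who declined further assessment".

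The Methods text around Fig. 1 refers every participant with impaired lung function for work-up, whether or not a lung condition was already known. Patients who cannot be seen at the clinic are told to contact their general practitioner.

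Statistical considerations specifies a Poisson regression of the contact rate on group, with potential confounders that are not listed. The later paragraph on medication ends: "Specifically, age, smoking history, and comorbidities will be included as covariates in our models".

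**The concern.** An impact of screening is a difference between what happens with screening and what would have happened without it. The plan asks that question, but its data contain only screened patients. Following it as written, a difference between attenders and decliners of work-up, or between new and known cases, would be read as the answer.

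At stake is the main 5-year conclusion. A lower or higher contact rate in group 1 could be reported as a result of nurse-led screening when it shows only how patients who take up assessment differ from those who do not. The prevalence objective is unaffected.

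**Working it through.** **1. The plan's own figure.** The stated sample size is 511, from a background prevalence of 4.3%, a doubling to 8.6%, 80% power and a significance level of 0.05. With the pooled two-sided formula for two proportions, mean 0.0645:

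n = [1.960 × √(2 × 0.0645 × 0.9355) + 0.842 × √(0.043 × 0.957 + 0.086 × 0.914)]² / 0.043² = (0.681 + 0.291)² / 0.001849 ≈ 511 per group.

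The figure reproduces, but it serves the prevalence comparison only. It has no bearing on the 5-year aim.

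**2. What each contrast can show.**

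| | Screened | Ratio below 0.7 | Referral rule applies | Defined by |
|---|---|---|---|---|
| Group 1 | yes | yes | yes | no earlier diagnosis, underwent assessment |
| Group 2 | yes | yes | yes | self-reported earlier diagnosis |
| Group 3 | yes | yes | yes | no earlier diagnosis, declined assessment |

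- Screening does not vary between the groups, so no coefficient in the model can represent it.
- Group 1 versus group 3 is a contrast of uptake after screening.
- Group 1 versus group 2 is a contrast of new against known disease, with both referred.
- Contacts are reported for each year after inclusion. No period before inclusion is described, so there is no before-and-after comparison either.
- For medication, the outcome section compares groups 1 and 2, while Statistical considerations compares no COPD with diagnosed COPD. These need reconciling, and neither version has an unscreened group.

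**3. How far uptake alone could move the result.** The documents give no inputs here; the values are assumptions. Suppose a factor multiplies the contact rate by R and is present in a share pA of attenders and pD of decliners. With no true difference, the apparent ratio is [1 + pA(R − 1)] / [1 + pD(R − 1)].

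| R | pA 0.3, pD 0.5 | pA 0.5, pD 0.3 |
|---|---|---|
| 1.5 | 1.15/1.25 = 0.92 | 1.25/1.15 = 1.09 |
| 2 | 1.30/1.50 = 0.87 | 1.50/1.30 = 1.15 |
| 3 | 1.60/2.00 = 0.80 | 2.00/1.60 = 1.25 |

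The direction is not known in advance.

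**4. The work-up visit as an outcome.** Outpatient visits with a COPD-related diagnosis count as contacts. If group 1 has one such visit because of the assessment itself, and the base rate is b contacts per year (assumed 0.5 to 2), the ratio with no other difference is (b + 1)/b = 3.0 to 1.5 in year 1, and (5b + 1)/(5b) = 1.4 to 1.1 over 5 years.

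**5. Room for covariates.** At 8.6%, 511 × 0.086 ≈ 44 patients have COPD. If 50–70% are undiagnosed and 30–70% of those attend (assumptions), groups 1 and 3 hold between 44 × 0.5 × 0.3 ≈ 7 and 44 × 0.7 × 0.7 ≈ 22 patients each. The hypothesis is at least a doubling, so 44 is the low end. At an assumed prevalence of 40% the same range is about 31 to 100.

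**The case against.** The strongest reply is that the study reports on whether there is an impact, labels its groups openly by who underwent and who declined assessment, says that social-nurse support must be considered in interpretation, and acknowledges selection bias. A condensed article may also leave the covariate list to a fuller document. All of this is fair, but it does not meet the point. The acknowledged selection is between sites and through exclusion of the acutely ill. Nothing mentions the absence of unscreened patients, and no covariate list can create them.

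The objection does rule out several stronger readings that a reader might infer:

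- **That the contact model omits severity and social confounders.** The model promises potential confounders without closing the list. Age, smoking history and comorbidities are named at the end of the medication paragraph, and not as the only ones.
- **That all three groups select themselves, for known reasons.** Group 2 is set by a reported earlier diagnosis. The documents do not say what drives acceptance; the one stated factor is whether a clinic visit is feasible.
- **That the CAT score is a ready covariate.** It is described for patients diagnosed with COPD. The Discussion hints at wider use, so its availability in groups 1 and 3 is uncertain.
- **That low power proves the point.** Any power figure here rests on assumed group sizes, contact rates and dispersion, and concerns precision rather than identification.
- **That mortality has been left out of the study.** Mortality data are to be obtained, and a condensed article need not set out that analysis.

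**Conclusion.** The concern holds as a matter of identification. The planned comparison cannot estimate an effect of opportunistic screening, because screening and the offer of referral are the same in all groups. At best, group 1 versus group 3 describes an association with uptake of assessment. This conclusion rests on the stated group definitions and referral rule, and needs no numerical assumption.

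The size of any distortion cannot be derived from the documents. The ratios of 0.80 to 1.25 from an unadjusted factor, and 1.1 to 1.4 over 5 years from one counted work-up visit, are illustrations under assumed values. The Abstract's survival statement is an expectation; it should not become a conclusion about screening.

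**What to change.** 1. Restate objective 2 and the 5-year outcomes as the association between uptake of further assessment (group 1 versus group 3) and later COPD-related contacts among screen-positive patients without an earlier diagnosis. Keep group 2 as a descriptive reference, and treat the medication comparison as descriptive once its two group definitions are reconciled.
2. Do not present group differences, or the survival expectation in the Abstract, as an effect of screening. State in the Discussion that there is no unscreened comparator.
3. Within the potential confounders of the contact model, name FEV1 % predicted, housing and AUDIT or drug use, all recorded at baseline, in a number that the group sizes can support. Add contacts in the year before inclusion if the register linkage covers that period, which the article does not state.
4. State whether the assessment visit itself counts as a contact.

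These covariates reduce confounding between groups 1 and 3 but do not stand in for unscreened patients. The cost is wording, slightly more analysis work and a more modest claim. No new baseline data are needed.

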## Material and methods

### Study setting

Study participants are identified during hospitalization at the participating hospitals, that is admission to emergency, medical and surgery departments, and recruited by social nurses, working at 11 hospitals within three of the five Danish regions (Capital Region of Denmark, Region Zealand, and Central Denmark Region). The hospitals include both urban and rural areas. Patient recruitment commenced on April 19th, 2021 and is still enrolling patients, with an anticipated completion of enrolment in 2024.

### Study subjects

The goal of this study is to include socially marginalized patients, who are individuals facing multiple and very challenging life circumstances such as mental health disorders, substance use disorder, and other complex issues like homelessness and involvement in criminal activities, in the target population of social nurses. This group comprises approximately 70,000 individuals in Denmark [17]. It is important to note that there is a significant utilization of healthcare services within this population, with 13% having been hospitalized in the past 3 months, and 16% having sought care from an emergency department [9]. Ultimately, it is the responsibility of the social nurse to determine whether the patient falls within the target group, resulting in a highly selected group of patients. The findings of this investigation, based on the questionnaire, will reveal whether the included patients align with the description that constitutes the target population of social nurses.

The study inclusion criteria for patients seen by a social nurse:Patients aged 18 years or olderPatients able to comply with study proceduresPatients able to understand Danish and provide informed consent

Exclusion criteria:Patients without a Danish civil registration number

The exclusion of patients without Danish civil registration numbers is because they only have access to acute medical care and cannot be followed up via the nationwide Danish health registries.

This study is conducted in accordance with ethical principles derived from international guidelines, including the Helsinki Declaration [9]. All participants will have to provide written informed consent.

The study protocol received approval from the Regional Ethics Committee (H-20031386, December 10, 2020) and is registered on ClinicalTrials.gov (reference NCT04754308, February 12, 2021). The collection and processing of data have been authorized by the Capital Region on behalf of the Danish Data Agency (P-2020-137).

### Study design

This is a prospective longitudinal study with 5 years follow-up from the date of inclusion.

The power calculation is based on the assumption that the prevalence of COPD will be twice the prevalence in the Danish background population (4.3%). With a power of 80% and a significance level of 0.05, a sample comprising 511 patients is required.

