### Data collection

#### Baseline

Baseline data are derived from lung function measurements and the interviews and questionnaires completed at inclusion.

The data is sampled online by social nurses using a smartphone or tablet, and the data is directly entered into REDCap (Research Electronic Data Capture) [19]. Further, the results of the spirometry are uploaded directly from the smartphone to REDCap.

If online data entry is not possible, a paper version of the survey will be available. At the end of the inclusion period, they will be sent to the Department of Clinical Research at Hvidovre Hospital and entered manually into REDCap.

Upon reaching the necessary number of participants, the local investigators will refer to the outpatient bookings and physician notes in the electronic patient record, to determine whether the participants underwent further evaluation at a department of respiratory medicine and if a diagnosis of COPD was confirmed (as indicated by ICD10 coding J44).

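### Groups 1 and 3 are split by an event after inclusion that has no time limit, while COPD contacts count from inclusion, so the contact-rate ratio can be pushed above 1 with no true effect

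*Protocol article*

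**What the plan says.** - **Time origin** (Study design): "This is a prospective longitudinal study with 5 years follow-up from the date of inclusion".
- **Outcome** (Five-year follow-up outcome measures): "number of hospital contacts per person year within each year of the 5-year follow-up (both outpatient visits and hospitalizations"), restricted to contacts with a COPD-related diagnosis. Statistical considerations divides contacts by follow-up length.
- **Assessed group** (same outcome section): "1) the group with no previous COPD diagnosis, impaired lung function at screening, and who underwent further assessment".
- **Unassessed group**, two wordings. The outcome section and the Fig. 1 caption use refusal: "3) the group with no previous COPD diagnosis, impaired lung function at screening, and who declined further assessment". Statistical considerations uses absence of assessment: "undiagnosed COPD at inclusion who underwent further assessment, undiagnosed COPD without further assessment, and previously diagnosed COPD at inclusion, using a Poisson regression model".
- **How assessment is determined** (Data collection, Baseline): "Upon reaching the necessary number of participants, the local investigators will refer to the outpatient bookings and physician notes in the electronic patient record", to see whether evaluation at a respiratory department took place. The article does not expressly say that this check assigns the five-year groups, but it describes no other way of determining assessment.
- **Recruitment** (Study setting): from 19 April 2021, expected to end in 2024.
- **A time window** appears once. Outcome measures lists, as a baseline proportion, patients examined at a clinic or GP within 4 months of screening. Neither group definition uses it.

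**The concern.** Group 1 against group 3 is the only contrast among screen-detected patients with and without work-up. It therefore carries most of the second objective, the five-year impact of screening and referral. Membership depends on something that happens after the clock has started, and the article gives no deadline for it. This has two consequences.

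1. A COPD admission long after screening may itself lead to a respiratory clinic visit. If status is read once at the end of recruitment, that patient counts as assessed, and the admission that caused the assessment counts against the assessed group. How far back the check looks also depends on the recruitment date.
2. The assessment visit takes place at a hospital outpatient clinic. If it is coded as COPD-related, it is an outcome event that group 1 can have and group 3 cannot.

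Both make assessed patients look worse. That could hide a benefit of work-up or suggest harm. Adjustment for age, smoking and comorbidities does not repair groups defined by later events.

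**Working it through.** **The plan's own figure.** The only computed figure is 511 patients, for the prevalence comparison. A pooled two-proportion formula (4.3% against 8.6%, two-sided 0.05, 80% power) gives 511.2, or 512 per group after rounding up. It has no bearing on this contrast, for which the article gives no contact rate or ratio.

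**Look-back length.** From 19 April 2021 to 1 January 2024 is 2.70 years (32.4 months). To 31 December 2024 it is 3.70 years (44.4 months). The first recruit thus has about 32 to 44 months in which to be found assessed, and the last has almost none.

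**Contact-triggered assessment, null simulation.** Assumed, not in the article: 0.5 COPD contacts per year on average; 40% assessed through the referral, at a uniform time within 4 months; time from inclusion to record check uniform on 0 to 3 years; mortality hazard 0.10 per year; 5 years of follow-up; no effect of assessment. Each contact leads to a clinic assessment with probability q. The assessment visit is not counted. Ratio = (contacts ÷ person-years, assessed) ÷ (contacts ÷ person-years, unassessed).

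| q | Read at end of recruitment, equal patient rates | Same, gamma rates (shape 1) | 4-month landmark, equal rates | 4-month landmark, gamma rates |
|---|---|---|---|---|
| 0 | 1.00 | 1.00 | 1.00 | 1.00 |
| 0.1 | 1.08 | 1.24 | 1.00 | 1.04 |
| 0.2 | 1.15 | 1.45 | 1.00 | 1.08 |
| 0.3 | 1.21 | 1.62 | 1.00 | 1.12 |

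If uptake of the referral is spread over a year instead of 4 months, the gamma-rate landmark ratios become about 1.12, 1.19 and 1.28. What remains is selection of frequent attenders, that is, confounding by severity.

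**Wider grid with equal rates.** Contact rate 0.2 to 1.0 per year, q 0.1 to 0.5, early uptake 30% or 50%, recruitment span 3.0 or 3.7 years, mortality 6% per year: 36 scenarios. Read at the end of recruitment, the null ratio is 1.06 to 1.57, and 2% to 40% of the assessed group enters after month 4. With the landmark it is 0.99 to 1.01.

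**Early death alone.** The q = 0 row gives 1.00. Across mortality of 5–20% per year and uptake over a year, the range is 0.97 to 1.00.

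**Assessment visit counted as an outcome.** With rate λ and follow-up T, and one extra contact per assessed patient, the null ratio is (λT + 1) ÷ λT = 1 + 1/(λT). For T = 5:
- λ = 0.2: 1 + 1/1.0 = 2.0
- λ = 0.5: 1 + 1/2.5 = 1.4
- λ = 1.0: 1 + 1/5.0 = 1.2

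With the 0.10 mortality hazard, mean follow-up is (1 − e^−0.5)/0.10 = 3.93 years, so λ = 0.5 gives 1 + 1/(0.5 × 3.93) = 1.51. This needs no contact-triggered assessment and holds under either wording of group 3, but only if the visit carries a COPD-related code.

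**The case against.** **The word used for group 3.** The outcome section and the Fig. 1 caption say that these patients declined. Declining is naturally a reply to the screening referral. A patient who refused and is admitted two years later has still refused, and does not move to group 1. If groups follow uptake of the referral, the null ratio is about 1.0 before the assessment visit is counted. This stands as a possible reading. But Statistical considerations, which defines the model, says without further assessment, and no recording of refusals is described. The wordings conflict, and the assessment-visit problem survives both.

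**The record check.** It stands under baseline data collection, and bookings carry dates, so one reading does not by itself mean an unlimited window. A reader might infer that the article fixes five-year status by this check regardless of date. It does not say so, and the triggered-contact bias is therefore conditional.

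**Early death.** A reader might also infer serious immortal-time bias, because patients who die early cannot be assessed. The figures do not support that.

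**Size.** The larger ratios need strong differences in rate between patients as well as an assumed 10–30% trigger probability. With equal rates the excess is about a third as large.

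**Reporting by year.** Results for each follow-up year would show part of the problem. With equal rates the triggered-contact distortion falls in years 1–3 and is about 1.00 in years 4–5; with gamma rates about 1.17–1.40 remains. The assessment visit is concentrated, not diluted: if it falls in year 1 at 0.5 contacts per year, that year's ratio is 1 + 1/0.5 = 3.0.

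**Left to the analysis plan.** Landmark details often are. Here, though, the article fixes the time origin, the grouping event, the outcome and the model, and together they create the bias.

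**Conclusion.** The point holds in a conditional form. As written, the contrast of group 1 with group 3 uses an event after inclusion without a time limit against contacts counted from inclusion, and the unassessed group is defined in two incompatible ways. The bias runs towards more contacts in the assessed group.

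Its size cannot be read from the article. With no true effect:
- about 1.1 to 1.6 if status is read at the end of recruitment and 10–30% of contacts lead to assessment (1.08 to 1.21 with equal rates, 1.24 to 1.62 with gamma shape 1);
- about 1.4 to 1.5 from one COPD-coded assessment visit per assessed patient at 0.5 contacts per year;
- near 1.0 if neither occurs.

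The prevalence objective and its sample size are unaffected. The medication comparison in the outcome section sets group 1 against group 2 and has no unassessed group, so the concern does not carry over to it in this form.

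**What to change.** 1. Use one definition of group 3 throughout, reconciling *declined* with *without further assessment*.
2. Classify groups 1 and 3 by assessment within 4 months of screening, the window already given under Outcome measures, using dated records.
3. Count contacts and person-time from month 4, among those alive and still under follow-up. Keep patients assessed later in the unassessed group.
4. Add a sensitivity analysis with assessment as a time-varying exposure.
5. State that the landmark removes the part of the bias made by the design, but not confounding by severity.

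The same time origin may be used for group 1 in the medication analysis, if wanted.

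Cost: a change of analysis wording, with no new data beyond dated bookings and the planned register linkage. The first 4 months and the early deaths leave this comparison and should be reported separately. First assessment visits after month 4 will count as contacts in the unassessed group, so their number should be reported too.
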